## Clinical Procedures

**Clinical measurements:** Blood pressure will be measured 3 times in a sitting position and the last 2 values averaged. Anthropometric measurements include height, weight, waist and hip circumference, and % body fat by bioimpedance (Tanita scale). In our previous study ([name], unpublished), we showed that the major results using this measurement did not differ significantly from those by DXA. Waist circumference is measured two times at the iliac crest and hip circumference is measured at the widest point of the hips.

**Blood sampling:** Using standard blood collection procedures, blood samples will be collected from participants after a 12-14 hour fast. The blood will be collected into tubes containing the following preservative solution: 3.0 gms EDTA (dipotassium), 1.7 mg P-Pack, 0.15 gms gentamycin sulfate, 0.15 gms chloramphenicol, 5.96 mls aprotinin (Sigma A-6279), and 0.30 gms sodium azide all of which are diluted to 20mls with

doubly deionized water. Plasma is separated by immediate centrifugation at 4°C. Lipid and lipoprotein measurements are performed as described below and aliquots of plasma are frozen for future analyses (8, 1ml each). Post-heparin plasma samples will be collected after a heparin bolus for lipase activity assays.

Plasma analyses: At the screening visit (V1), plasma will be analyzed for total cholesterol, LDL-cholesterol, HDL-cholesterol, triglycerides, glucose, TSH, and LDL peak particle size for LDL phenotype determination. At V2a and V3a (first visits before and after randomized diet), measurements will include total cholesterol, LDL-cholesterol, HDL-cholesterol, triglycerides, apolipoprotein A1 and B, LDL phenotyping, lipoprotein subfraction analysis by ion mobility, CETP activity, and post-heparin HL and LPL activity. We will also collect white blood cells and buffy coats for future genetic analyses. A portion of the white blood cells will be immortalized to generate permanent cell lines. At visits V2b and V3b (second visits before and after randomized diet), measurements will include total cholesterol, LDL-cholesterol, HDL-cholesterol, triglycerides, and lipoprotein subfraction analysis by ion mobility. The blood-drawing schedule is shown in **Figure 5**.

Adverse event reporting. At each blood draw visit, a registered nurse will discuss with the participant any adverse events that may have occurred and will note any events in the visit record. A registered nurse will also be available by phone to discuss any events that occur during the study. All non-serious events will be documented in an event tracking log, individually reviewed by the PI, and reported to the IRB per policy. Serious or unexpected adverse events will be reported per IRB policy and will be documented in the participant's chart and database record.

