## Data Analysis

The hypothesis that increased saturated fat derived primarily from dairy products will increase levels of large HDL2 and large LDL in pattern B individuals, with no significant effect on small, dense LDL, will be tested by comparing the mean change in large LDL levels as measured by ion mobility. The statistical significance will be evaluated by one-way analysis of variance with the factor being high or low saturated fat intake. Similar analyses will be used to test the effects of saturated fat on HDL cholesterol, and LDL diameter. Comparison of LDL pattern conversion rate between high and low saturated fat diets will be analyzed by Chi-squared analysis.

**Table 1** shows the detectable and expected differences using data from the high fat/low fat study described above [27]. Expected differences are derived from correlations of the change in fatty acid intake (assessed by food records of prescribed diets) and change in LDL measurements. The correlations were used to select the differences in SFA (12%), myristic (2.5%), and palmitic acid (5.5%) levels needed for a detectable effect in the primary endpoints given 25 subjects per group. These are approximately equal to the mean change in intake in our previous study. With 25 subjects/group, we have adequate power (80%) to detect the expected changes in LDL I, LDL diameter, and HDL2b given either a 12% difference in saturated fat or a 2.5% difference in myristic acid between the two diets. Although the lipoprotein subfraction predictions are based on measurements made by analytical ultracentrifugation or gradient gel electrophoresis, we expect the ion mobility method to be equally or more

precise. Typical standard deviations for measurements by ion mobility are 20.9 mg/dl for large LDL and 3.5 Å for LDL diameter. In addition, we will use the average value of measurements from two blood draws on consecutive days to reduce variance and increase power.

**Table 1:** Detectable (80% power) and expected difference for primary endpoints

|               | SD of difference | Detectable differences between groups  |            | Expected Difference w/ 12% ΔSFA | Expected Difference w/ 2.5% Δ14:0 |
|---------------|------------------|----------------------------------------------------|------------|---------------------------------|-----------------------------------|

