|               |                  | Difference                                         | % baseline |                                 |                                   |
| HDL2b (mg/dl) | 11.5             | 6.5                                                | 25         | 7.9 mg/dl                       | 10.7 mg/dl                        |
| LDL-I (mg/dl) | 29.6             | 16.6                                               | 22         | 39.2 mg/dl                      | 49.6 mg/dl                        |
| LDL diam (Å)  | 5.0              | 2.9                                                | 1.7        | 4.9 Å                           | 6.1 Å                             |

Detectable differences assume the average of 2 baseline and 2 post-diet measurements

To estimate predicted LDL pattern conversion rates, we used logistic regression to achieve a best approximation of the expected conversion rate between the two diets. At 35% carbohydrate intake and 12% difference in saturated fat, we expect that 48% pattern B participants will convert to pattern A. With a 2.5% difference in myristic acid, we predict a 71% conversion rate. Similar power estimates were obtained with a 5.5% difference in palmitic acid.

Other endpoints will include plasma triglyceride, total cholesterol, LDL-cholesterol, HDL cholesterol, apoB, apoAI, and LDLII-IV. **Table 2** presents the detectable differences in these endpoints estimated at 80% statistical power, 5% significance using baseline concentrations and standard deviation of response observed in our previous controlled dietary trials. Detectable differences are in accordance with power estimates from previous diet studies.

Sample size estimation is determined by lipoprotein endpoints, as not enough data is available to estimate expected differences in CETP, HL, and LPL activity levels. Based on previous data, we have adequate power (86%) to detect a difference of 15% baseline levels of HL activity between groups and reasonable power (52%) to detect a difference of 30% baseline levels of LPL between groups.

**Table 2.** Detectable differences (80% power) in other plasma lipid and lipoprotein levels

|                            | Baseline concentrations | Standard deviation of difference | Differences between groups         |            |
|----------------------------|-------------------------|----------------------------------|------------------------------------|------------|

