|                            |                         |                                  | Detectable Difference  | % baseline |
| Triglycerides (mg/dL)      | 215.31±106.34           | 117.97                           | 65.98                              | 30.65      |
| Total cholesterol (mg/dL)  | 206.79±32.53            | 25.97                            | 14.52                              | 7.02       |
| LDL-chol(mg/dL)            | 127.55±30.19            | 24.60                            | 13.76                              | 10.79      |
| HDL-C(mg/dl)               | 36.49±6.05              | 5.34                             | 3.05                               | 8.36       |
| Apo AI (mg/dL)             | 109.21±14.17            | 9.49                             | 5.31                               | 4.87       |
| Apo B (mg/dL)              | 99.78±18.03             | 25.50                            | 14.26                              | 14.29      |
| LDL-2 (mg/dL)  | 90.03±38.62             | 35.00                            | 19.58                              | 21.75      |
| LDL-3 (mg/dL)  | 91.33±28.76             | 25.02                            | 13.99                              | 15.31      |
| LDL-4 (mg/dL)  | 18.72±14.39             | 15.71                            | 8.78                               | 46.92      |

Detectable differences assume the average of 2 baseline and 2 post-diet measurements

LDL subfraction data for this table was derived from a more recent study than data shown in Table 1, but show very similar % baseline differences.

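### Table 2 credits apo AI and apo B with two-draw averaging although the visit schedule assays them once per diet phase; the apo AI figure is understated, and the apo B figure also depends on a doubtful SD

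*Protocol*

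**What the plan says.** The Plasma analyses paragraph (Protocol, section 4, Clinical Procedures) sets out the assays by visit. The list for the first visit of each pair, V2a and V3a, contains "triglycerides, apolipoprotein A1 and B, LDL phenotyping, lipoprotein subfraction analysis by ion mobility, CETP activity". For the second visit it says: "At visits V2b and V3b (second visits before and after randomized diet), measurements will include total cholesterol, LDL-cholesterol, HDL-cholesterol, triglycerides, and lipoprotein subfraction analysis". Neither apolipoprotein is in that second list.

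In the Data Analysis section, apo B and apo AI are among the other endpoints, and Table 2 is introduced as giving "detectable differences in these endpoints estimated at 80% statistical power, 5% significance", based on the "standard deviation of response observed in our previous controlled dietary trials". Footnote 1 is attached to the heading of the detectable-difference column and so covers every row: "Detectable differences assume the average of 2 baseline and 2 post-diet measurements". For apo AI the table gives baseline 109.21±14.17, SD of difference 9.49 and detectable difference 5.31 mg/dL (4.87% of baseline). For apo B it gives 99.78±18.03, 25.50 and 14.26 mg/dL (14.29%).

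**The concern.** The schedule provides one apolipoprotein measurement per diet phase, while the table takes credit for two. If the schedule is followed, the two tabled differences are too small for 80% power.

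This matters most when a null result is read. In the Background, the absence of an apo B effect in an earlier study is taken as evidence that LDL composition changed while particle number did not. Anyone repeating that reasoning here would need to know how large an apo B difference the trial could have missed.

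A second oddity sits in the same table. The apo B SD of difference is what two uncorrelated measurements would give, although the text says the SDs were observed.

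**Working it through.** **Inputs.** Power 80% and 5% significance (Data Analysis; two-sided assumed, since sidedness is not stated). Sample size: "given 25 subjects per group". Test: "one-way analysis of variance with the factor being high or low saturated fat intake", which with two groups is the two-sample t-test on change. SDs and differences are from Table 2.

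**Step 1: reproduce the stated figures.** Detectable difference = (1.960 + 0.842) × SD × √(2/25) = 0.792 × SD for one draw. Dividing the SD by √2 for two draws gives 0.560 × SD.

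| | SD | Stated | Stated/SD | Two draws, 0.560 × SD | One draw, 0.792 × SD |
|---|---|---|---|---|---|
| Apo AI | 9.49 | 5.31 | 0.5595 | 5.32 | 7.52 |
| Apo B | 25.50 | 14.26 | 0.5592 | 14.29 | 20.21 |

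The stated values match the two-draw column. Triglycerides, total cholesterol, LDL cholesterol and LDL-2 to LDL-4, all scheduled at both draws, have the same ratio of 0.559 (HDL cholesterol has 0.571). The full two-draw reduction was therefore applied to the apolipoprotein rows.

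**Step 2: one draw per phase.** With the noncentral t on 48 degrees of freedom, the single-draw factor is 0.8087.

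- Power at the stated difference (about 0.559 SD): 49.1% for each analyte; 50.7% by the normal approximation.
- Apo AI at 80% power: 0.8087 × 9.49 = 7.67 mg/dL; 7.67/109.21 = 7.0% of baseline.
- Apo B at 80% power, taking 25.50 as given: 0.8087 × 25.50 = 20.62 mg/dL; 20.62/99.78 = 20.7% of baseline.
- With all 64 enrolled analysed (32 per group), power at the stated differences would still be only about 60%.

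**Step 3: check the apo B SD.** √2 × 18.03 = 25.498, which rounds to the tabled 25.50. With equal variances before and after, SD of difference = SD × √(2(1 − r)), so r = 1 − (SD of difference)²/(2 × SD²). This gives r = 0 for apo B. The other rows give 0.38 (triglycerides) to 0.78 (apo AI), with LDL cholesterol at 0.67 and total cholesterol at 0.68.

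**Step 4: how far the apo B result depends on that SD.** Single-draw power at 14.26 mg/dL reaches 80% when the SD of change is 14.26/0.8087 = 17.63, that is, when r = 1 − 17.63²/(2 × 18.03²) = 0.52. If r were 0.67 (an assumption borrowed from the LDL cholesterol row), the SD would be 18.03 × √0.66 = 14.65, the detectable difference 11.9 mg/dL and the power at 14.26 about 92%.

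**Step 5: what a second assay would restore.** If the whole variance of change were within-person and independent between days, power at the stated values would return to about 78% (t) or 80% (normal). If half of it were, power would be about 61% to 63%.

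**The case against.** The strongest reply concerns apo B. If 25.50 is not an observed SD it is probably too large, and 49% and 20.6 mg/dL, which both use it, need not hold. That stands: Step 4 shows that a pre/post correlation of about 0.52, lower than most rows of the table imply, would remove the apo B shortfall on a single draw. Equally, the match with √2 × 18.03 is an inference from one ratio. The source trials cannot be seen, so it supports a query and does not prove a misstatement.

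It can also be said that the visit lists may not be exhaustive: CETP mass is described under Laboratory procedures but is in neither list, the Data Analysis text states two-draw averaging in general terms, and the visit figure is not shown. This has some weight, but the second list repeats the lipids and ion mobility and leaves out the apolipoproteins, and nothing else schedules a repeat apolipoprotein assay.

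Three stronger readings are tempting, and the documents do not support them.

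- That the stated differences cannot be reached at all. Blood is drawn at V2b and V3b, so a second assay is possible.
- That the 86% and 52% powers for HL and LPL share the fault. They are stated apart from the tables, as based on previous data, with no mention of averaging.
- That the particle-number conclusions rest on apo B. The trial's three hypotheses make no apo B claim, and ion mobility, described as quantifying particles directly, is run at both draws.

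**Conclusion.** The schedule and Table 2 cannot both stand for these two rows. For apo AI the correction is firm, given that the tabled SD is a single-draw SD, which is how the table treats it: 7.7 mg/dL in place of 5.31, and about 49% power at the stated difference. For apo B the averaging credit is equally unsupported, but 20.6 mg/dL is conditional on an SD that must first be traced to its source; the true shortfall may be smaller or absent. Severity is minor to moderate: neither analyte drives the sample size, and the primary endpoints are measured at both draws.

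**What to change.** First, trace the apo B SD of 25.50 to its source and, if it was not observed, replace it with the SD of change that was. Then reconcile the schedule and the table in one of two ways.

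- **Restate the rows.** Remove footnote 1 from apo AI and apo B and give single-draw values: about 7.7 mg/dL for apo AI, and 0.809 times the verified SD for apo B. This costs a table edit.
- **Add the assays.** Measure apo AI and apo B on plasma already drawn at V2b and V3b, and add them to the visit list. This is four extra assays per participant (two analytes at two visits) and no extra blood draw. The apo B row must still be recalculated if its SD changes, and the text should say that the full gain depends on the variance of change being within-person and independent between days.

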## **Laboratory procedures**

Lipid analyses. Human plasma will be analyzed for concentrations of total cholesterol [37] and triglyceride [38], and for high density lipoprotein (HDL)-cholesterol, measured directly after precipitation of apolipoprotein B containing lipoproteins in plasma [39]. LDL cholesterol is calculated by subtraction of estimated VLDL and measured HDL cholesterol from the measured total cholesterol and triglyceride in plasma. Lipid assays are enzymatic end-point measurements utilizing enzyme reagent kits (Ciba-Corning Diagnostics Corp., Oberlin, Ohio) and a CIBA Corning Express 550 automated analyzer. The measurements are standardized through the CDC-NHLBI Lipid Standardization Program.

Apolipoprotein B and AI : Immunoturbidimetric assay [40, 41] will be used to measure apolipoproteins AI and B in human plasma samples. Reagents, standards, and reference plasma controls, with and without elevated lipids, are included in the ITA reagent kit (Bacton Assay Systems, Inc., San Marcos, CA). Measurements will be performed using the Express Plus 550 analyzer. Calibrators and reference controls are assigned concentration values with the use of International Federation of Clinical Chemistry standard reference materials SP1 for apoAI and SP3-07 for apoB.

Lipoprotein subclass analysis by ion mobility (IM). LDL and HDL subfractions will be analyzed using our in-house method, ion mobility (IM), which uniquely allows for direct particle quantification following an ultracentrifugation to remove albumin. The IM instrument utilizes an electrospray to create an aerosol of particles, which then pass

through a dynamic mobility analyzer (DMA) coupled to a particle counter [29]. Particle diameter and quantity are determined and converted to lipoprotein mass and LDL peak particle size. Interassay variation is reduced by inclusion of two in-house controls in each preparatory process.

Hepatic and lipoprotein lipase activity. Total hepatic (HL) and lipoprotein lipase (LPL) activity will be measured in post-heparin plasma samples by incubation with a standard concentration of isotope-labeled esterified fatty acids (glycerol tri[H]-oleate) followed by quantification of extracted free fatty acids using a liquid scintillation counter [42]. HL activity is determined using selective inhibition with protamine sulfate. LPL activity will be calculated as the difference between total post-heparin lipase activity and HL activity.

Cholesterol ester transfer protein (CETP) activity. CETP activity will be measured by a commercially available activity assay kit (Roar Biomedical, Inc) according to manufacturer's recommendations [43, 44]. In-house frozen control plasmas will be used to monitor assay variability.

Cholesterol ester transfer protein (CETP) mass. Plasma concentrations of CETP protein will be measured by ELISA using a commercially available kit (Alpco Diagnostics) according to kit instructions. In-house frozen control plasmas will be used to monitor assay variability.

Plasma glucose. Glucose will be measured using enzymatic reagent kits (Glucose HK Reagent, Ciba Corning Diagnostics) and interassay variation will be monitored by using in-house frozen control plasmas.

Thyroid stimulating hormone. Plasma thyroid stimulating hormone (TSH) will be sent to Quest Diagnostics for analysis.

## Data Analysis

The hypothesis that increased saturated fat derived primarily from dairy products will increase levels of large HDL2 and large LDL in pattern B individuals, with no significant effect on small, dense LDL, will be tested by comparing the mean change in large LDL levels as measured by ion mobility. The statistical significance will be evaluated by one-way analysis of variance with the factor being high or low saturated fat intake. Similar analyses will be used to test the effects of saturated fat on HDL cholesterol, and LDL diameter. Comparison of LDL pattern conversion rate between high and low saturated fat diets will be analyzed by Chi-squared analysis.

**Table 1** shows the detectable and expected differences using data from the high fat/low fat study described above [27]. Expected differences are derived from correlations of the change in fatty acid intake (assessed by food records of prescribed diets) and change in LDL measurements. The correlations were used to select the differences in SFA (12%), myristic (2.5%), and palmitic acid (5.5%) levels needed for a detectable effect in the primary endpoints given 25 subjects per group. These are approximately equal to the mean change in intake in our previous study. With 25 subjects/group, we have adequate power (80%) to detect the expected changes in LDL I, LDL diameter, and HDL2b given either a 12% difference in saturated fat or a 2.5% difference in myristic acid between the two diets. Although the lipoprotein subfraction predictions are based on measurements made by analytical ultracentrifugation or gradient gel electrophoresis, we expect the ion mobility method to be equally or more

precise. Typical standard deviations for measurements by ion mobility are 20.9 mg/dl for large LDL and 3.5 Å for LDL diameter. In addition, we will use the average value of measurements from two blood draws on consecutive days to reduce variance and increase power.

**Table 1:** Detectable (80% power) and expected difference for primary endpoints

|               | SD of difference | Detectable differences between groups  |            | Expected Difference w/ 12% ΔSFA | Expected Difference w/ 2.5% Δ14:0 |
|---------------|------------------|----------------------------------------------------|------------|---------------------------------|-----------------------------------|
|               |                  | Difference                                         | % baseline |                                 |                                   |
| HDL2b (mg/dl) | 11.5             | 6.5                                                | 25         | 7.9 mg/dl                       | 10.7 mg/dl                        |
| LDL-I (mg/dl) | 29.6             | 16.6                                               | 22         | 39.2 mg/dl                      | 49.6 mg/dl                        |
| LDL diam (Å)  | 5.0              | 2.9                                                | 1.7        | 4.9 Å                           | 6.1 Å                             |

Detectable differences assume the average of 2 baseline and 2 post-diet measurements

To estimate predicted LDL pattern conversion rates, we used logistic regression to achieve a best approximation of the expected conversion rate between the two diets. At 35% carbohydrate intake and 12% difference in saturated fat, we expect that 48% pattern B participants will convert to pattern A. With a 2.5% difference in myristic acid, we predict a 71% conversion rate. Similar power estimates were obtained with a 5.5% difference in palmitic acid.

Other endpoints will include plasma triglyceride, total cholesterol, LDL-cholesterol, HDL cholesterol, apoB, apoAI, and LDLII-IV. **Table 2** presents the detectable differences in these endpoints estimated at 80% statistical power, 5% significance using baseline concentrations and standard deviation of response observed in our previous controlled dietary trials. Detectable differences are in accordance with power estimates from previous diet studies.

Sample size estimation is determined by lipoprotein endpoints, as not enough data is available to estimate expected differences in CETP, HL, and LPL activity levels. Based on previous data, we have adequate power (86%) to detect a difference of 15% baseline levels of HL activity between groups and reasonable power (52%) to detect a difference of 30% baseline levels of LPL between groups.

**Table 2.** Detectable differences (80% power) in other plasma lipid and lipoprotein levels

|                            | Baseline concentrations | Standard deviation of difference | Differences between groups         |            |
|----------------------------|-------------------------|----------------------------------|------------------------------------|------------|
|                            |                         |                                  | Detectable Difference  | % baseline |
| Triglycerides (mg/dL)      | 215.31±106.34           | 117.97                           | 65.98                              | 30.65      |
| Total cholesterol (mg/dL)  | 206.79±32.53            | 25.97                            | 14.52                              | 7.02       |
| LDL-chol(mg/dL)            | 127.55±30.19            | 24.60                            | 13.76                              | 10.79      |
| HDL-C(mg/dl)               | 36.49±6.05              | 5.34                             | 3.05                               | 8.36       |
| Apo AI (mg/dL)             | 109.21±14.17            | 9.49                             | 5.31                               | 4.87       |
| Apo B (mg/dL)              | 99.78±18.03             | 25.50                            | 14.26                              | 14.29      |
| LDL-2 (mg/dL)  | 90.03±38.62             | 35.00                            | 19.58                              | 21.75      |
| LDL-3 (mg/dL)  | 91.33±28.76             | 25.02                            | 13.99                              | 15.31      |
| LDL-4 (mg/dL)  | 18.72±14.39             | 15.71                            | 8.78                               | 46.92      |

Detectable differences assume the average of 2 baseline and 2 post-diet measurements

LDL subfraction data for this table was derived from a more recent study than data shown in Table 1, but show very similar % baseline differences.

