(no activity was measured) in the saturated fat diet, but no increase in HDL [26]. However, this study was conducted on a background of a 47% carbohydrate diet and it may be that carbohydrate content modifies the effects of saturated fat. Our previous studies observing increases in HDL and large LDL were performed on a background of a lower carbohydrate intake. Other possible mechanisms that can result in increases in both large HDL and LDL include a reduction in hepatic lipase (HL) activity or an increase in lipoprotein lipase (LPL) activity, and again there is a lack of evidence regarding the effects of saturated fat on these enzyme activities.

We and others have consistently shown that decreases in dietary carbohydrate intake to levels below that of the typical American diet can reduce levels of LDL cholesterol, independent of body weight, even when accompanied by high intakes of saturated fat. This reduction in LDL cholesterol is specifically due to a decrease in small, dense, LDL particles in a manner that is independent of saturated fat intake (**Figure 1** and [3]). We recently demonstrated that a higher (15%) vs. lower (9%) saturated fat content in diets containing 26% carbohydrate and 29% protein increased both HDL cholesterol and total LDL mass and that this was associated with a non-significant increase in large LDL without a change in small LDL. Furthermore, there were no effects of increased saturated fat intake on apoB levels, indicating a change in composition, but not in total number of LDL particles.

**Figure 1.** Left panel: Changes in mass of total LDL and LDL subfractions (large=LDL I, medium=LDL II, and small=LDL III+IV) with reduced carbohydrate intake in 178 overweight and obese men. Right panel: Changes in HDL cholesterol. Changes are in reference to the baseline diet (54% carbohydrate, 16% protein, 30% fat, 7% saturated, 13% monounsaturated). After

one week on the baseline diet subjects were randomized to 4 weeks of the baseline diet, or diets with reduced content of carbohydrate (39% or 26% together with increased protein (29%)). For the lowest carbohydrate intake (26%), there was also an increase in fat intake (45%), achieved either with low saturated fat (9% saturated, 27% monounsaturated or high saturated fat (15% saturated, 20% monounsaturated). Body weight was constant.

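### The hypothesis includes non-significance on small, dense LDL, but a non-significant result would not show that the LDL rise is selective

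*Protocol*

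**What the plan says.** The opening sentence of Data Analysis gives a two-part hypothesis: large HDL2 and large LDL rise, "with no significant effect on small, dense LDL, will be tested by comparing the mean change in large LDL levels". The method follows: "The statistical significance will be evaluated by one-way analysis of variance with the factor being high or low saturated fat intake". Similar analyses are announced for HDL cholesterol and LDL diameter, and a chi-squared test for pattern conversion. None of these is a test of small LDL.

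Small LDL is defined in the Figure 1 legend (Background, effect of saturated fat on lipoprotein metabolism) as "small=LDL III+IV". Its components appear among the secondary measures: "Other endpoints will include plasma triglyceride, total cholesterol, LDL-cholesterol, HDL cholesterol, apoB, apoAI, and LDLII-IV". Table 2 gives LDL-3 and LDL-4 detectable differences "estimated at 80% statistical power, 5% significance", with the footnote "Detectable differences assume the average of 2 baseline and 2 post-diet measurements". No margin or interval criterion is given for small LDL.

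The interpretation leans on this component. The Background attributes the saturated-fat effect to larger LDL particles not related to cardiovascular risk, and the Project Design overview expects the increase in large LDL to be selective.

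**The concern.** Failing to reject a null hypothesis is not evidence for it. If the small-LDL clause is judged as worded, imprecision helps it: the noisier the measurement or the smaller the sample, the more likely the clause appears to hold. If only the test named in the sentence is run, the clause is not examined at all, because a difference in large LDL says nothing about small LDL.

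What is at stake is the reading of the main result. A rise in large LDL is presented as benign because it is expected to be confined to large particles. That reading needs evidence on how large a rise in small LDL has been ruled out, and a p-value above 0.05 does not supply it.

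**Working it through.** **Inputs (Data Analysis, Table 2).**
- LDL-3: baseline 91.33 mg/dl, SD of difference 25.02, detectable difference 13.99 (15.31%).
- LDL-4: baseline 18.72 mg/dl, SD of difference 15.71, detectable difference 8.78 (46.92%).
- Design: "given 25 subjects per group", 80% power, 5% significance (taken as two-sided, which reproduces the table).
- Source of the SDs: "LDL subfraction data for this table was derived from a more recent study than data shown in Table 1". They are borrowed values.

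**1. Reproducing Table 2.** With the variance halved for duplicate draws, detectable difference = (1.960 + 0.842) × (SD/√2) × √(2/25) = 0.560 × SD.
- LDL-3: 0.560 × 25.02 = 14.02 (stated 13.99).
- LDL-4: 0.560 × 15.71 = 8.80 (stated 8.78).

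Without halving, the results are 19.83 and 12.45. A one-sample formula with n = 25 gives the same 14.02 and 8.80, so the arithmetic alone does not prove that halving was used, but the averaging footnote points to it. Full halving requires all variance of the change to be independent between the two draws. Stable differences between people in their response would not average out. Results below therefore run from SD/√2 (favourable) to the printed SD (averaging removes nothing). Both ends are extremes.

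**2. Precision.** 95% half-width = t(0.975, 48) × SD × √(2/25) = 2.011 × 0.2828 × SD.

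| | SD/√2 | printed SD |
|---|---|---|
| LDL-3 | 10.1 mg/dl (11.0%) | 14.2 mg/dl (15.6%) |
| LDL-4 | 6.3 mg/dl (33.7%) | 8.9 mg/dl (47.7%) |

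An LDL-3 result just short of significance has an upper limit of twice the half-width: 20.1 to 28.5 mg/dl, or 22% to 31% of baseline.

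**3. Chance of a non-significant result when LDL-3 truly rises.** Noncentral t, 48 degrees of freedom, noncentrality = rise / (SD × √(2/25)).

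| True rise | Noncentrality, SD/√2 | Non-significant | Noncentrality, printed SD | Non-significant |
|---|---|---|---|---|
| 10% (9.13 mg/dl) | 1.825 | 57% | 1.291 | 76% |
| 15% (13.70 mg/dl) | 2.738 | 24% | 1.936 | 52% |

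**4. LDL III+IV combined.** Baseline 91.33 + 18.72 = 110.05 mg/dl. SD = √(25.02² + 15.71² + 2ρ × 25.02 × 15.71). The protocol does not give the correlation ρ, so it is assumed here.

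| ρ (assumed) | SD | Half-width, SD/√2 | Half-width, printed SD |
|---|---|---|---|
| -0.3 | 25.24 | 10.15 (9.2%) | 14.35 (13.0%) |
| 0 | 29.54 | 11.88 (10.8%) | 16.80 (15.3%) |
| 0.3 | 33.30 | 13.39 (12.2%) | 18.94 (17.2%) |
| 0.5 | 35.58 | 14.31 (13.0%) | 20.23 (18.4%) |

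**5. What the trial could exclude.** The protocol gives no margin, so these are illustrative. Normal approximation, one-sided 2.5%, true difference zero: power = Φ(margin / (SD × √(2/25)) − 1.960).
- LDL-3 rise of 10%: 45% (SD/√2) or 25% (printed SD).
- LDL-3 rise of 15%: 78% or 49%.
- LDL-3 rise of 20%: 96% or 73%.

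**The case against.** The case on the other side has several parts.

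- **No decision rule is spelled out.** Nowhere does the protocol say that a non-significant small-LDL test confirms anything. That is correct. The point rests on the wording of the hypothesis and on the mismatch with its named test.
- **Small LDL is not a formal objective.** The three hypotheses in Research Project Objectives and Hypothesis cover coordinate increases in large HDL and large LDL, pattern conversion and a common pathway. None requires a null effect on small LDL, which sits among the other endpoints. This limits the weight of the point but does not remove it, because the Background and the design overview still rely on selectivity.
- **Other measures bear on the LDL change.** LDL diameter, pattern conversion and apoB all inform it. None of them estimates the change in small LDL.
- **Interval reporting and margins usually belong in the SAP.** That is fair, and their absence is no finding. The wording of the hypothesis is the protocol's own.

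A reader might also infer three stronger things. The first is that the plan uses non-significance as proof of safety, but small LDL is given no safety role; the protocol speaks of selectivity and lower atherogenicity. The second is that the trial cannot exclude any sizeable rise. The protocol sets no threshold for sizeable, and under halved variance with a true difference of zero the trial has 78% power to exclude a 15% LDL-3 rise and 96% for 20%. The third is that the very wide LDL-4 interval describes small LDL as a whole. LDL-4 is 18.72 of 110.05 mg/dl, or 17%, so a 20% rise in it (3.74 mg/dl) is about 3.4% of small LDL.

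**Conclusion.** The point holds as one of wording and inference. The protocol makes non-significance on small, dense LDL part of its hypothesis, names only a large-LDL difference test for it, and gives no basis for reading a null result as selectivity. Under Table 2's own favourable variance, a true 10% rise in LDL-3 would still be non-significant more often than not. The weakness is greatest for LDL-3 rises of about 10% or less. For rises of 15% to 20%, it depends on how much variance the duplicate draws remove.

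The figures assume 25 completers per group, two-sided 5%, and borrowed SDs that carry over to ion mobility. The combined LDL III+IV figures also rest on the assumed correlations. The primary comparison of large LDL is not affected.

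**What to change.** In Data Analysis, remove the absence of a significant small-LDL effect as a criterion. Name LDL III+IV, as defined in the Figure 1 legend, as the small-LDL measure. Analyse its between-arm difference in change and report it with a 95% confidence interval. Base any statement about selectivity on which increases that interval excludes. Claim no effect only against a margin that is justified and written down before outcomes are compared by arm; otherwise report small LDL as inconclusive. The protocol supplies no basis for a margin, so none is suggested here.

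The cost is a change of wording, plus a margin if a no-effect claim is wanted. No extra participants, visits or assays are needed. The downside is that, at this sample size, the small-LDL result may have to be reported as inconclusive.
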